## Abstract

**Background:**

In well-child care it is difficult to determine whether preschool children with asthma symptoms actually have or will develop asthma at school age. The PIAMA (Prevention and Incidence of Asthma and Mite Allergy) Risk Score has been proposed as an instrument that predicts asthma at school age, using eight easy obtainable parameters, assessed at the time of first asthma symptoms at preschool age. The aim of this study is to present the rationale and design of a study 1) to externally validate and update the PIAMA Risk Score, 2) to develop an Asthma Risk Appraisal Tool to predict asthma at school age in (specific subgroups of) preschool children with asthma symptoms and 3) to test implementation of the Asthma Risk Appraisal Tool in well-child care.

**Methods and design:**

The study will be performed within the framework of Generation R, a prospective multi-ethnic cohort study. In total, consent for postnatal follow-up was obtained from 7893 children, born between 2002 and 2006. At preschool age the PIAMA Risk Score will be assessed and used to predict asthma at school age. Discrimination (C-index) and calibration will be assessed for the external validation. We will study whether the predictive ability of the PIAMA Risk Score can be improved by removing or adding predictors (e.g. preterm birth). The (updated) PIAMA Risk Score will be converted to the Asthma Risk Appraisal Tool- to predict asthma at school age in preschool children with asthma symptoms. Additionally, we will conduct a pilot study to test implementation of the Asthma Risk Appraisal Tool in well-child care.

**Discussion:**

Application of the Asthma Risk Appraisal Tool in well-child care will help to distinguish preschool children at high- and low-risk of developing asthma at school age when asthma symptoms appear.

This study will increase knowledge about the validity of the PIAMA risk score and might improve risk assessment of developing asthma at school age in (specific subgroups of) preschool children, who present with asthma symptoms at well-child care.

## Background

Asthma symptoms in preschool children are non-specific. It is therefore difficult to determine which preschool children with asthma symptoms actually have or will develop asthma at school age
[1]. A recent study has shown that both undertreatment and overtreatment of asthma in children between ages 2 and 8 years seem common
[2]. Inadequate risk assessment of asthma when children present with asthma symptoms at well-child care may be an important cause of inadequate treatment of childhood asthma. To improve early diagnosis and management of asthma symptoms, we reasoned that early detection of preschool children at high risk of developing asthma at school age is important.

In this study we present the rationale and design of a study focusing on risk assessment of asthma in well-child care. Well-child care physicians and nurses have routine contact with about 90% of all preschool children and their families
[3] and therefore can play an important role in 1) early detection of children with asthma symptoms in the general population, 2) risk assessment of asthma in early detected children and 3) adequate monitoring and counselling of children at high risk of asthma. The first and third step are currently being studied in a randomised controlled trial ‘to evaluate the effectivity of early detection and counselling of preschool asthma symptoms within well-child care’
[4]. However, the second step of asthma risk assessment in children who are detected early in life is not yet available within well-child care. There is a need for an Asthma Risk Appraisal Tool to support well-child care professionals when a preschool child presents with asthma symptoms.

To estimate the risk of developing asthma at school age at the time children have asthma symptoms in preschool years, a risk score (i.e. prediction model) may be a suitable tool. A tool like this could support the communication between well-child care professionals and parents of children at risk of developing asthma. Several studies previously developed a prediction model for asthma
[5-12]. It is complicated to compare these studies, because definitions and age of asthma differed. Many studies used information up to a fixed age, irrespective of the age of symptom onset
[6,8,10,11]. The PIAMA (Prevention and Incidence of Asthma and Mite Allergy) Risk Score has been proposed as an instrument that predicts asthma at age 7–8 years, using eight easy obtainable parameters, assessed at the time of first asthma symptoms at preschool age
[7]. The PIAMA Risk Score discriminated between asthmatic and non-asthmatic children (internally validated area under the curve, AUC = 0.72) and may be a suitable tool for use in well-child care. Prediction models are mathematical models based on available patient data from a certain setting. Before use of a prediction model can be recommended in practice, external validation is mandatory to determine the ability of a model to reliably predict the outcome in other populations and settings
[7].

The main objective is to present the rationale and design of a study to externally validate and update the PIAMA Risk Score. Furthermore, an Asthma Risk Appraisal Tool will be developed to predict asthma at school age in (specific subgroups of) preschool children with asthma symptoms. We will conduct a pilot test of the Asthma Risk Appraisal Tool within well-child care.

By describing the rationale and design of our study we give insight into the framework of our study. This framework concerns the process of external validation and updating of a prediction rule, development of an application tool and assessment of whether the tool can be implemented into practice. This study will help others to convert prediction rules into practice.

## Methods and design

### Design and setting

Our study will be embedded in Generation R, a prospective population-based, multi-ethnic cohort study. In total, consent for postnatal follow-up was obtained from 7893 children, born between April 2002 and January 2006
[13]. Questionnaires for parental completion, partly based on the International Study of Asthma and Allergies in Childhood (ISAAC) core questionnaires
[14], were sent to the parents during pregnancy and when the children were aged 1, 2, 3, 4 and 6 years (N=7893)
[15]. Response rates for these questionnaires were 71%, 76%, 72%, 73% and 68% respectively. Data collection at child’s age of 9 years is currently ongoing. In this study, children will be included if at least one positive response was given to the following questions in the annual questionnaires at age 1 to 4 years: “Has your child had wheezing in the last 12 months?” and “Has your child had cough during the night, when he/she did not have a cold or a chest infection, in the last 12 months?” The present study was conducted in accordance with the guidelines proposed in the Declaration of Helsinki, and is approved by the Medical Ethical Committee of the Erasmus Medical Centre (MEC 217.595/2002/202). Written consent was obtained from all participating parents.

### Asthma outcomes

The outcome that is predicted with the PIAMA Risk Score is asthma at school age. In the development study (PIAMA) the following 3 items were used for the case definition of asthma: (1) at least 1 episode of wheezing in the last 12 months; (2) inhaled steroids prescribed by a medical doctor in the last 12 months; and (3) a doctor’s diagnosis of asthma (a parental report of a doctor’s diagnosis of asthma at any time and a parental report of asthma in the last 12 months). In the analyses children were only considered positive for asthma if they had 1 or more positive items at age 7 years and 1 or more positive items at age 8 years
[7].

Within the validation data (Generation R), we aim to use the same asthma definition as used in PIAMA and we aim to select only children with ‘active asthma’ or clinically relevant chronic asthma symptoms. First, we will define asthma at the age of 6 years in the children who have ever had reported asthma symptoms before the age of 4 years. Additionally, the analyses will be repeated in children at age 9 years. At age 9 years spirometry will be performed in children at the research center. Spirometry is used to improve the accuracy of an asthma diagnoses and will be enable us to compare asthma outcomes based on parental reports to asthma outcomes based on spirometry.

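### The promised PIAMA asthma definition needs positive items at ages 7 and 8; Generation R outcomes at 6 and 9, analysed separately, cannot meet it, so the calibration intercept mixes model error with a change of endpoint

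*Protocol article*

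**What the plan says.** All references are to the protocol article, Methods and design.

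- **Asthma outcomes, PIAMA rule.** There are three items: a wheezing episode, prescribed inhaled steroids, and a doctor's diagnosis of asthma. A child counted as a case only "if they had 1 or more positive items at age 7 years and 1 or more positive items at age 8 years". The Background section agrees: the score "has been proposed as an instrument that predicts asthma at age 7–8 years".
- **Asthma outcomes, Generation R rule.** The next paragraph states the aim: "we aim to use the same asthma definition as used in PIAMA and we aim to select only children with". The sentence then limits cases to children whose disease is currently active, and adds "or clinically relevant chronic asthma symptoms" as the alternative. No item rule is given for that restriction. It continues: "First, we will define asthma at the age of 6 years in the children who have ever had reported asthma symptoms" before age 4. The analyses are then repeated at age 9.
- **Design and setting.** Questionnaires "were sent to the parents during pregnancy and when the children were aged 1, 2, 3, 4 and 6 years". Age-9 collection is under way. No contact at 7 or 8 is listed.
- **External validation.** The outcome distributions of the two cohorts are compared first. Calibration-in-the-large is then estimated with the PIAMA predictions as an offset. A non-zero intercept is read as predictions that are systematically too low or too high.
- **Updating.** The updated score is fitted to the two cohorts combined.
- **Discussion.** Design and analysis are said to differ little between the development and validation studies.

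**The concern.** The PIAMA rule demands persistence over two consecutive years. A single-age outcome has no persistence requirement, and the ages differ as well. The article therefore promises a definition that the data it describes cannot deliver, and names no substitute.

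This matters because external validation is the first aim. The calibration intercept compares the observed outcome frequency with risks estimated for the PIAMA endpoint. If the endpoints differ, a model that transports perfectly can show a non-zero intercept, and a model that transports badly can show an intercept near zero. The plan has no step that separates the two sources.

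The problem carries forward. As written, the combined fit would put a two-age endpoint and a one-age endpoint in the same regression. Its coefficients would describe neither, and the appraisal tool is built from that updated score.

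**Working it through.** **1. The plan's own figure.** Sample size: 3967 symptomatic children × 5% assumed asthma prevalence at age 6 = 198.35, stated as about 198. It reproduces. The 5% is a single-age figure.

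**2. Can the PIAMA rule be met?** It needs items at 7 and at 8. The ages available are 6 and 9, used one at a time. It cannot.

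**3. Effect if the same items are used at one age.** Let P1 be the proportion positive at one age, and q the chance of being positive at the second age given the first. The two-age proportion is P2 = q × P1. Suppose the PIAMA model predicts P2 correctly, and single-age prevalence is the same at the ages compared. Then:

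- observed/expected = P1/P2 = 1/q
- marginal intercept shift ≈ logit(P1) − logit(P2)

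The documents give neither q nor the PIAMA prevalence. The assumed range is q = 0.4 to 0.9. The shift is shown twice: with the article's 5% as P1 (so P2 = 0.05q), and with an assumed P2 of 10% (so P1 = 0.10/q).

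| q | O/E = 1/q | Shift, P1 = 5% | Shift, P2 = 10% | Two-age cases, 198 × q |
|---|---|---|---|---|
| 0.9 | 1.11 | +0.11 | +0.12 | 178 |
| 0.8 | 1.25 | +0.23 | +0.25 | 158 |
| 0.7 | 1.43 | +0.37 | +0.41 | 139 |
| 0.6 | 1.67 | +0.53 | +0.59 | 119 |
| 0.5 | 2.00 | +0.72 | +0.81 | 99 |
| 0.4 | 2.50 | +0.95 | +1.10 | 79 |

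Example: q = 0.5 and P1 = 5% give P2 = 2.5%, and logit(0.05) − logit(0.025) = −2.944 + 3.664 = 0.72.

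**4. Against sampling error.** Assume the 68% age-6 response applies to the symptomatic children: 3967 × 0.68 = 2698. At 5% prevalence the intercept SE is roughly 1/√(2698 × 0.05 × 0.95) = 0.088. A shift of +0.11 (q = 0.9) is about 1.25 SE and could pass unnoticed. A shift of +0.95 (q = 0.4) is more than 10 SE.

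**5. Effect of the active-asthma restriction.** If it keeps only a share s of single-age positives, O/E = s/q. At q = 0.7, s = 1.0, 0.7 and 0.5 give 1.43, 1.00 and 0.71. The sign depends on s, which the article does not define.

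**6. Events under a two-age rule.** The Sample size section asks for at least 100 cases. If all 198.35 expected age-6 cases were observed, positivity at a second age must satisfy q ≥ 100/198.35 = 0.50. With 68% response, 198.35 × 0.68 = 134.9, and q ≥ 100/134.9 = 0.74. For a 6-and-9 rule, q is the chance of being positive at 9 given positive at 6.

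**The case against.** The strongest case on the other side has four parts.

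- **Direction.** A reader might infer that the Generation R outcome is simply looser, that one wheezing episode at age 6 makes a case, and that the study will report underprediction. The article does not say so. The restriction to active or chronic disease sits in the same sentence as the promise and may be meant to stand in for persistence. Step 5 shows it could cancel or reverse the shift. True prevalence may also change between ages 6, 7–8 and 9. This objection stands. It does not rescue the wording, because a tightened single-age rule is not the PIAMA definition either.
- **Updating and discrimination.** A reader might infer that the plan resets the intercept to a less specific outcome, or that the C-index will be diluted. The Updating section describes removing and adding predictors, refitting and pooling; it names no intercept-update step. No figure in the article supports a claim about discrimination. Neither inference is made here.
- **Existing safeguards.** Outcome distributions are compared before validation, the ages are openly disclosed, and age-9 parental reports will be set against spirometry. These may reveal a gap. None of them separates definition from model error or harmonises the combined fit.
- **Softened promise and condensed format.** The wording states an aim, and a fuller document may hold the exact item rule. That excuses the missing detail. It does not excuse stating sameness when the ages on the page rule it out.

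**Conclusion.** The point holds as a definitional mismatch. The article says the PIAMA definition will be used, its own description of the data shows that it cannot be, and both the calibration intercept and the combined fit depend on the two endpoints being the same.

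The size is conditional. Using the same items at one age, a perfectly valid model would show observed/expected of 1.11 to 2.5 for q from 0.9 to 0.4, an intercept shift of about +0.1 to +1.1 in the two scenarios tabulated. This rests on an assumed q, equal single-age prevalence across the ages compared, and no effect of the active-asthma restriction. Relaxing the last assumption can bring the ratio below 1. The documents therefore do not establish that calibration will be biased in a particular direction. They do establish that the intercept, as planned, cannot be attributed to the model.

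**What to change.** 1. In Asthma outcomes, drop the claim of sameness for the single-age analyses. State the Generation R case rule, including what the active-asthma restriction requires, and qualify the Discussion's remark on small design differences.
2. The combined fit already calls for the PIAMA data. Use them to re-estimate the PIAMA model, at least its intercept, for a single-age outcome with the same items, and judge Generation R calibration against that version. If this is not possible, report the intercept but do not attribute it to the model.
3. Use one common outcome rule for both cohorts in the combined fit.
4. When age-9 data are in, add positivity at both 6 and 9 as a sensitivity analysis only. It spans three years, so it is not the PIAMA rule either.

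**Cost.** Revised wording and modest extra analysis, with no new data collection. A one-year age difference remains after step 2 (for example 7 against 6). The 6-and-9 outcome loses children without both follow-ups and may fall below the plan's 100-case minimum, so its event count should be checked first.

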### Preschool predictors

The eight predictor variables used in the PIAMA Risk Score are: 1) sex, 2) post-term delivery, 3) parental education, 4) parental inhalation medication, 5) child’s wheezing frequency, 6) wheezing/dyspnea apart from colds, 7) serious infections and 8) doctor’s diagnosis of eczema and eczematous rash present. The variables wheezing/dyspnea apart from colds and parental inhalation medication are not available within the Generation R Study at preschool age. For parental inhalation medication a proxy variable of parental asthma is available. Information on sex and pregnancy duration are obtained from medical records; parental education and asthma are established using questionnaires during pregnancy; wheezing frequency, respiratory tract infections and eczema are measured using questionnaires at the ages of 1, 2, 3 and 4 years.

### External validation

As a first step we will compare the distribution of the predictors of the PIAMA Risk Score and the asthma outcome in the development (PIAMA) and validation (Generation R) data to determine whether the datasets are comparable. Univariate logistic regression analyses will be performed to establish the effect of the different predictors on asthma at the age of 6 and 9 years. The resulting univariate odds ratios (ORs) will be compared with ORs in the development sample as reported for the PIAMA model. Next, the multivariate PIAMA model will be fitted in the validation sample to compare the multivariate ORs. Finally we will calculate the predicted probability to develop asthma for each child in the validation sample, based on the PIAMA score. These predicted probabilities are used to assess the external validity of the PIAMA model, in terms of calibration and discrimination. Calibration refers to the agreement between observed and predicted outcomes. The extent of over- or underestimation relative to the observed and predicted rate will be explored graphically using validation plots. We will assess calibration-in-the-large by fitting a logistic regression model with the model predictions as an offset variable. The intercept indicates whether predictions are systematically too low or too high, and should ideally be zero. The calibration slope reflects the average effects of the predictors in the model and will be estimated in a logistic regression model with the logit of the model predictions as the only predictor. For a perfect model, the slope is equal to 1. The Concordance-index (C-index) or Area Under the receiver operating characteristic Curve (AUC) and 95% confidence interval (CI) will be used to assess the ability of the model to discriminate children with and without asthma. The external validation will also be performed in specific subgroups (e.g. at different ages or in ethnic and socioeconomic subgroups of preschool children, see subgroup analysis). To interpret any differences in C-indices, we will consider benchmark values as recently proposed
[16].

### Updating

After external validation we will assess whether the predictive performance of the PIAMA model remains stable or improves by deleting or adding predictors that are available in the validation data.

By removing predictors, a more simple risk score will be created. The predictive performance of such a simple risk score will be compared with the predictive performance of the PIAMA Risk Score. A simpler risk score is preferable for application in practice
[17]. Potential additional predictors include e.g. child’s ethnicity, preterm birth, sleeping problems due to asthma symptoms, doctor visits due to asthma symptoms, wheezing patterns, allergy or general health. To study the prognostic value of additional predictors, we will refit the PIAMA Risk Score in the validation data and consequently add the new predictors. We will calculate the increase in AUC with 95% CI, and the p-value from the likelihood ratio test for improvement of goodness of fit. This will result in an updated PIAMA Risk Score. For optimal precision of the estimated coefficients, the updated PIAMA Risk Score will be fitted to the combined PIAMA and Generation R data.

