### Pilot testing

After development of the Asthma Risk Appraisal Tool, the tool will be tested in a pilot study within well-child care. The pilot test will be conducted in the Rotterdam-Rijnmond area that contains both rural and metropolitan and ethnically diverse sub-regions. The implementation will involve 3 varied well-child care teams (including one or more well-child care physicians, nurses and medical assistants per team that provide services to a certain group of preschool children in a distinct geographical region). It is aimed to pilot the Asthma Risk Appraisal Tool to 100 children/families. So, a total of 300 children/families are aimed to be included in the pilot study.

When children present with asthma symptoms, the Asthma Risk Appraisal Tool will be applied. In the pilot study we will assess how many preschool children were detected as high-risk of developing asthma at the ages of 6 and 9 years by the Asthma Risk Appraisal Tool. We will evaluate which decisions cq. actions were taken by physicians/nurses after the use of the Asthma Risk Appraisal Tool (and how many times). Evaluation of the effectivity of implementation of the Asthma Risk Appraisal Tool in well-child care practice is outside the framework of this study.

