## Discussion

We present the rationale and design of a study to externally validate and update the PIAMA Risk Score and to develop and test an application of the PIAMA Risk Score to predict asthma at school age in (specific subgroups of) preschool children with asthma symptoms. This Asthma Risk Appraisal Tool might be used in well-child care as an Asthma Risk Appraisal Tool in preschool children already detected with asthma symptoms.

Several studies previously developed a prediction model to predict asthma
[5-12]. It is complicated to compare these studies, because definitions and age of asthma differs and it is unknown which definition of asthma truly identifies the disease. Many studies used information up to a fixed age irrespective of the age of symptom onset
[6,8,10,11]. Some of the prediction models included blood tests
[6,11,12]. Prediction models including blood tests are not feasible in well-child care, given the (very) low acceptance of drawing blood in the setting of prevention by parents and children, the lack of funding for laboratory tests in preventive healthcare, and because laboratory results should be awaited. Therefore, the PIAMA Risk Score - including only easy obtainable parameters - is preferred above prediction models including blood tests. The PIAMA Risk Score has been compared to the asthma predictive index developed by Castro-Rodriquez et al.
[6] and showed a better predictive ability, and also performed better than a doctors diagnosis of asthma at the same age
[7].

This study benefits from a longitudinal design, which enables us to collect repeated measurements of predictors at preschool age. In this way we can identify the age at onset of first symptoms, unlike some earlier studies who predict asthma at fixed ages
[6,8,10,11]. The ages at which asthma symptoms appear most frequently is the time that children will regularly visit well-child care and when prediction of asthma becomes relevant. Furthermore, there will be little differences in design and analysis between the development and the validation study. It is our intention to develop an Asthma Risk Appraisal Tool integrated in well-child care at preschool age in such a way that it has maximal opportunity for future wide-spread implementation, once proved useful.

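### Updating: candidate predictors are admitted if they are in the data, and wheezing patterns are named, with no limit to what is known when the child is scored at first symptoms

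*Protocol article*

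**What the plan says.** **When the child is scored.** The Background describes the PIAMA Risk Score as eight parameters "assessed at the time of first asthma symptoms at preschool age". The Discussion part of the Abstract says that the tool will help to "distinguish preschool children at high- and low-risk of developing asthma at school age when asthma symptoms appear". Under Pilot testing the rule is: "When children present with asthma symptoms, the Asthma Risk Appraisal Tool will be applied".

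**How predictors enter the update.** The Updating section will examine whether performance holds or improves by "deleting or adding predictors that are available in the validation data". Its examples of additional predictors include child's ethnicity, preterm birth and symptom-related sleeping problems, and end with "doctor visits due to asthma symptoms, wheezing patterns, allergy or general health". None has a stated measurement time, and wheezing patterns are not defined. The yardstick is: "We will calculate the increase in AUC with 95% CI, and the p-value from the likelihood ratio test".

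**What is measured when.** Preschool predictors says that "wheezing frequency, respiratory tract infections and eczema are measured using questionnaires at the ages of 1, 2, 3 and 4 years". This covers items of the existing score, not the added candidates.

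**What follows.** The updated score becomes the Asthma Risk Appraisal Tool, and its cut-offs are to be studied within the validation study (Development of asthma risk appraisal tool).

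**The concern.** A prediction model can use only what is known at the moment of prediction. Here that moment is the onset of symptoms, and both the Background and the Discussion contrast this with models that collect information up to a set age whatever the age at onset. The admission rule in Updating is different: it asks whether a variable exists in Generation R, not whether it exists when the child is scored. Wheezing patterns are the named candidate for which the two questions ordinarily have different answers.

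If a pattern is built from questionnaires after the index one, its contribution to the AUC and to the likelihood ratio comes partly from follow-up. Neither measure can detect this. The updated score would be reported with a discrimination that it does not have in use, and its coefficients and cut-offs would be tuned to an input that staff at the well-child visit must leave empty or fill with an incomplete value. Predicted risks at presentation could then be systematically off, and the cut-offs are meant to lead to referral and counselling decisions.

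**Working it through.** **1. The plan's own figure.** The plan gives no figure on this point. The nearest is the expected number of cases at age 6 under Sample size: 3967 × 0.05 = 198.35, stated as about 198. It reproduces, and nothing below depends on it beyond the 5% prevalence.

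**2. Questionnaires still to come at first symptoms.** Children enter on a positive wheeze or night-cough answer at age 1, 2, 3 or 4 (Design and setting). With first report at age *k*, 4 − *k* preschool questionnaires lie in the future:

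| First report at age | Later preschool questionnaires |
|---|---|
| 1 | 3 |
| 2 | 2 |
| 3 | 1 |
| 4 | 0 |

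A pattern over ages 1 to 4 is complete at scoring only for children first symptomatic at 4. The article does not give the numbers by age of first report.

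**3. The candidates one by one.** Ethnicity and preterm birth are fixed at birth. Sleeping problems, doctor visits, allergy and general health can each be read from the index questionnaire. Only wheezing patterns, on the ordinary meaning, need repeated observation.

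**4. What could happen if the pattern spans ages 1 to 4 (illustration; everything but the 5% is assumed).** A simulation generated 400,000 children per scenario, of whom about 310,000 had at least one wheeze year and were kept.

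- Yearly wheeze at ages 1 to 4: logit P = *c* + *u*, with *c* = 0.1, −0.5, −0.9, −1.2 and *u* a standard normal persistence trait.
- Asthma: logit P = *a* + 0.8*x* + *b·u*, with *x* a standard normal score known at first symptoms and *a* set to give 5%.
- Base model: *x* and age at first wheeze. Its AUC is about 0.71, against the published 0.72 (Background).
- Pattern model: the base model plus the number of wheeze years over ages 1 to 4.
- Pattern model in use: the same coefficients with the count set to 1, as known at first symptoms.

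| *b* | Base AUC | AUC with full pattern | Apparent gain | AUC of pattern model at first symptoms | Mean predicted risk at first symptoms (observed 5.0%) |
|---|---|---|---|---|---|
| 0 | 0.710 | 0.710 | 0.000 | 0.710 | 5.0% |
| 0.4 | 0.708 | 0.713 | 0.004 | 0.707 | 4.1% |
| 0.8 | 0.708 | 0.729 | 0.021 | 0.703 | 3.2% |
| 1.2 | 0.706 | 0.749 | 0.043 | 0.694 | 2.5% |

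Gains are from unrounded values. In the strongest case the apparent gain of 0.043 becomes a loss of 0.706 − 0.694 = 0.012 in use, and predicted risk is 2.5/5.0 = half of that observed.

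**5. Limits of the illustration.** About 60% of the simulated children wheezed in more than one year, which is a consequence of the assumptions. The score *x* is drawn independently of *u*, whereas the real score contains wheezing frequency, which may well correlate with persistence; the gain may then be smaller. The table shows the direction, not the size to expect in Generation R.

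**The case against.** The strongest case against is that the article never says that later information will be used. Wheezing patterns appear once, undefined, among examples of potential predictors, and could mean a feature recorded at a single questionnaire. The Discussion says that the longitudinal design "enables us to collect repeated measurements of predictors at preschool age" and presents this as the way to identify age at onset, so the intention is to anchor at first symptoms. Pilot testing speaks of presentation with symptoms without the word first, so some children may arrive with a history. The article prefers a simpler score, which weighs against inputs that are hard to obtain. It also condenses a fuller plan, where measurement windows may be set.

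Much of this stands, and it rules out several stronger readings that a reader might infer:

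- *That the other candidates, or the original predictors, are taken from later waves.* No section says so. Preschool predictors lists data sources, and all four questionnaires are needed if first symptoms can occur at any of them.
- *That a pattern will be selected.* The article reports an AUC increase and a test but gives no automatic selection rule.
- *That the gain would be 0.02 to 0.09.* Such figures arise from adding a persistence indicator with 25% prevalence and odds ratios of 2 to 6, independent of a score that already contains wheezing frequency. None of those inputs is in the article.

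What the objection does not remove is the admission rule. The article does more than omit a detail: it states a criterion, availability in the data, and names a candidate that on its ordinary meaning conflicts with the stated moment of prediction. The onset anchoring in the Discussion is not carried into Updating. If the tool may also be used at later episodes, the need to name the index questionnaire is greater.

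**Conclusion.** The point holds in a limited form. As written, the Updating section can credit a wheezing pattern with information that is unavailable when the child is scored at first symptoms, and can carry it into the tool and its cut-offs. This rests on reading wheezing patterns as a summary over repeated yearly questionnaires and on use at first symptoms. It does not extend to the other listed candidates, for which the article gives no sign of later measurement, nor to the external validation of the existing score, which does not use the added candidates.

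The size cannot be derived from the article. Under the assumptions shown, the apparent AUC gain runs from none to about 0.04. In use there is no gain or a small loss, and mean predicted risk lies between correct and half of that observed. The change is worth making before the update is run because it is cheap and because neither planned yardstick would reveal the problem afterwards.

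**What to change.** Add to Updating that every candidate predictor takes its value from the questionnaire at which symptoms are first reported, or from an earlier one. Then do one of three things with wheezing patterns: drop them from the list, define them from information up to and including that questionnaire, or confine them to a separately labelled model for use at age 4, with its performance reported apart from that of the first-symptom tool.

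The cost is one sentence and a data-extraction rule, with no new data, since the Discussion says that age at onset can be identified. The downside is a possibly smaller apparent AUC gain from the update.
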